### Interim analysis

One interim analysis will be run after the enrolment of the 33^rd ^patient, which will be representative of half of the sample. This analysis will focus on the primary outcome and safety issues. Using the O'Brien-Fleming criteria for two-sided test, the alpha-level of this interim analysis will be 0.005. The final analysis will be conducted using an alpha-level of 0.048.

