#### Primary Outcome Measures

The primary outcome measure will be the change from baseline on the total score of the EAT-26 score measured at week 12 prior to topping off the medication, and BMI change over the first 12 weeks of treatment.

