### Sample Size

Given the relative novelty of this application of olanzapine, no formal evaluation of the drug has yet been conducted on youth, making it difficult to accurately estimate sample size requirements. However, after consultation within our clinical team we believe that a decrease of 5 points on the EAT-26 scale would be clinically meaningful. The following assumptions were therefore used for sample size calculations: i) a minimal clinical important difference of 5 on the EAT-26 score; ii) an estimated standard deviation of 7.07; iii) two-sided test; iv) a power of 80% and a type I error of 5%; v) a provision for one interim analysis according to the O'Brien and Fleming criteria [35]. With these assumptions, the total sample size necessary is 64 participants. Anticipating a drop-out rate of at most 2.5%, the formula of Donner [36] may be used to adjust the sample size assuming an intention to treat analysis. The resulting total sample size is thus 67 participants (33 and 34 participants per treatment group). We anticipate that this study will take two years to complete enrollment.

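### The interim analysis is triggered by the 33rd enrolment, but its 0.005 level fits 33 patients with week-12 outcomes; at the trigger itself only about 25 would have them

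*Protocol article*

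**What the plan says.** The Interim analysis section of the protocol article sets the timing by recruitment: "One interim analysis will be run after the enrolment of the" 33rd patient, "which will be representative of half of the sample". On content it says "This analysis will focus on the primary outcome and safety issues". It names the two-sided O'Brien-Fleming criteria and fixes both levels: "the alpha-level of this interim analysis will be 0.005", and "The final analysis will be conducted using an alpha-level of 0.048".

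Under Primary Outcome Measures, the first primary outcome is "the change from baseline on the total score of the EAT-26 score measured at week 12"; the second is BMI change over the same 12 weeks. The Sample Size section needs 64 participants, raised to 67 for drop-out, and adds: "We anticipate that this study will take two years to complete enrollment".

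No section says that the interim waits until the first 33 patients have reached week 12. The last-value imputation under Statistical Analysis covers participants who withdraw or are lost to follow-up before week 12. It does not cover participants who are still within their 12 weeks.

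**The concern.** An O'Brien-Fleming level depends on the fraction of the final information available at the look. For an outcome measured 12 weeks after randomization, that fraction is set by the number of patients with a week-12 value, not by the number enrolled. Everyone enrolled in the last 12 weeks before the trigger lacks the outcome, whatever the accrual rate. Followed as written, the trigger therefore gives a look at less than half the information, tested at a level meant for half.

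What is at stake is the strictness of the early look. O'Brien-Fleming boundaries are chosen so that a trial stops early only on very strong evidence, and a level that is too lenient for the information in hand weakens that protection. There is also a gap in procedure: with no stated rule on whether to wait, or on what to do with patients still in progress, the choice could be made once data exist.

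**Working it through.** **Inputs.** From the protocol article: interim trigger at the 33rd enrolment and levels 0.005 and 0.048 (Interim analysis); outcome at week 12 (Primary Outcome Measures); 64 evaluable and 67 enrolled participants, with enrolment over two years (Sample Size). Assumptions made here: even accrual over 104 weeks, and an analysis run at the trigger on patients who have reached week 12.

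**Step 1: reproduce the stated levels.** For two looks with information fraction *t* at the first, the O'Brien-Fleming critical values are *c*/√*t* at the interim and *c* at the final. The constant *c* solves P(|Z₁| > *c*/√*t* or |Z₂| > *c*) = 0.05, where Z₁ and Z₂ are standard normal with correlation √*t*. At *t* = 0.5:

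- *c* = 1.977, and *c*/√0.5 = 2.797
- two-sided levels 0.0052 (interim) and 0.0480 (final)

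These round to the stated 0.005 and 0.048, so the plan's levels assume half information.

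**Step 2: patients with the outcome at the trigger.**

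- Accrual rate: 67/104 = 0.644 per week
- Enrolled in the last 12 weeks: 12 × 0.644 = 7.7
- With a week-12 value: 33 − 7.7 = 25.3, about 25

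If the 67 patients accrue over 18 months instead, about 10.3 are still short of week 12 and about 23 have the outcome. Over 36 months, about 5.2 are short and about 28 have it.

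**Step 3: information fraction.** 25/67 = 0.373; with the 64 evaluable participants as denominator, 25/64 = 0.391. For comparison, 33/67 = 0.493 and 33/64 = 0.516.

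**Step 4: the level that belongs to each fraction, and the overall error if 0.005 and 0.048 are kept.** The last column is P(|Z₁| > 2.807 or |Z₂| > 1.977) under the null hypothesis, with correlation √*t*.

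| Patients with outcome | *t* | O'Brien-Fleming interim level | O'Brien-Fleming final level | Overall two-sided alpha with 0.005/0.048 |
|---|---|---|---|---|
| 33 of 67 | 0.493 | 0.0049 | 0.0481 | 0.0500 |
| 33 of 64 | 0.516 | 0.0058 | 0.0478 | 0.0498 |
| 25 of 67 | 0.373 | 0.0013 | 0.0495 | 0.0507 |
| 25 of 64 | 0.391 | 0.0017 | 0.0493 | 0.0506 |
| 23 of 67 (18-month accrual) | 0.343 | 0.0008 | 0.0497 | 0.0509 |
| 28 of 67 (36-month accrual) | 0.418 | 0.0023 | 0.0490 | 0.0504 |

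The Lan-DeMets spending function of O'Brien-Fleming type gives nearly the same interim levels: 0.0013 at *t* = 0.373 and 0.0017 at *t* = 0.391.

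**Step 5: ratio.** 0.005/0.0013 = 3.8 and 0.005/0.0017 = 2.9, so the stated level is about three to four times too lenient for the look with 25 patients.

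**The case against.** The strongest reply is that the wording places the analysis after the 33rd enrolment, not on that day. An analysis of a week-12 outcome might be taken to imply waiting for it. If all 33 are followed to week 12, the fraction is 0.49 and the stated levels fit, which suggests that this is what was meant. A condensed article may also leave the exact data cut-off to the full protocol. This stands in part: the benign reading is possible, and 25 is the number only if the analysis is run at the trigger. But the article does not state a wait, and it attaches the half-sample description to the enrolment point itself. A trigger and a threshold that are both stated, and that do not match when followed literally, are more than missing detail.

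The second reply is that the consequence is small. This stands fully. A reader might infer from a threshold three to four times too lenient that the trial's type I error is badly inflated. The table shows otherwise: the excess is under 0.001 in every row.

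Three further inferences are tempting and are not supported:

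- That the interim would be diluted by carrying forward early values of patients still in progress. The last-value rule covers only withdrawn or lost participants, so this is not the plan's procedure.
- That the half-sample description is simply false. The 33rd of 67 enrolled is half of the sample by head count; the mismatch is with information on the week-12 outcome.
- That low power at the interim is a defect. A first O'Brien-Fleming look is meant to have low power, and a stricter level would lower it further.

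**Conclusion.** The concern holds as a mismatch between the stated trigger and the stated interim level, and it should be fixed. That patients enrolled in the preceding 12 weeks lack the outcome at the trigger does not depend on any accrual assumption. The figure of about 25 does: it needs even accrual at the planned pace and no wait after the trigger. The documents support a wrong nominal level for one look and an ambiguity about when that look takes place. They do not support a claim that overall error control fails.

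**What to change.** Reword the Interim analysis section so that the interim is triggered when the 33rd randomized patient has completed week 12 or withdrawn before it. State that patients still awaiting week 12 at that time are left out of the interim efficacy comparison. With that wording, 0.005 and 0.048 can stay as they are.

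Add that, if the interim is run at any other information fraction, both levels will be recomputed with an O'Brien-Fleming-type (Lan-DeMets) spending function. This is a safeguard; it is not needed if the trigger is corrected and kept.

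The cost is a change of wording, an interim about 12 weeks later, and about 8 more patients enrolled by then (12 × 0.644 = 7.7). The wording should be settled before any interim data are examined.

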### Reporting

The Consolidated Standards of Reporting Trials (CONSORT) statement [37,38] will be used as a guideline for the present clinical trial in order to assure high quality reporting.
